**Table 2.1: Schedule of Assessments at each site.**

## **2.11 Clinical and laboratory assessments**

### **2.11.1 Demographic information**

Demographic information that will be collected will include age, sex, place of residence, marital status, level of education and employment status.

### **2.11.2 Medical History**

A detailed medical history will be taken from the patients by the study doctor. Some of the information to be taken will include when patient diagnosed with HIV, ARV regimen to be initiated, co- medications taken and/or to be initiated and information on some risk factors for cardiovascular disease (tobacco use/ smoking, hypertension, diabetes, physical inactivity and family history of cardiovascular disease). Also, information on history of active or previous peptic ulcer disease, epigastric pain, vomiting blood, passing blood in stools or black stools will be sought at enrollment and the follow up visits. The information will be obtained from the patients themselves, their files and/or treatment charts.

### **2.11.3 Clinical examination**

Blood pressure, height and weight measurements and a thorough examination of the respiratory system, lymphatic system, skin and mucous membranes, gastrointestinal tract (GIT), cardiovascular, central nervous system and musculoskeletal systems will be conducted by a study doctor at enrolment and at each follow up visit except for height measurement which will only be done at visit 0.

### **2.11.4 Weight, Height and Blood pressure measurements**

Weight will be measured using an analogue scale without shoes and will be recorded to the nearest 0.5 kg. Height will be measured by a wall-mounted tape-measure with a scale up to 0.1 cm and then converted to meters. Weight in kg will then be divided by height in meters squared to obtain BMI. BMI will be categorized into groups according to World Health Organization (WHO) criteria.

Blood pressure will be measured after the respondent has rested for at least 5 minutes, using a manual sphygmomanometer. The subject's left arm will be placed at the heart level. Two measurements will be taken at an interval of five minutes between readings. Patient's blood pressure will be the average of the two readings.

### **2.11.5 Urine Pregnancy Test**

At screening, all the female participants will be given urine containers to provide urine.

A urine for pregnancy test will be performed using a commercial kit for analysis of a urine sample for Human Chorionic Gonadotrophin (HCG) and the results will be interpreted according to the manufacturer's instructions.

### **2.11.6 Laboratory tests**

Laboratory tests for CD4 count at 3 months, lipid profile, FBP, RFT and LFT will be performed at the MUHAS Clinical Research laboratory (MCRL) at MUHAS. HIV viral load test at baseline, 2 and 3 months will be performed at the Central Pathology Laboratory at the Muhimbili National Hospital while HIV viral load and CD4 count at month 6 will be performed at the respective study sites laboratories. Plasma levels of sCD14, sP- selectin and biomarkers of T cell activation and exhaustion will be done in a laboratory at Kumamoto University, Japan.

- HIV Viral load testing will be performed using Abbott m 2000 rt (Applied biosystems ®, Singapore) with the lowest detection limit of 45 copies/ ml.
- Lipid profile, RFT and LFT will be performed using COBAS Integra 400 Plus (Roche Instruments Center AG, Switzerland)
- FBP will be performed using Sysmex (Sysmex Corporation, Japan)
- CD4 counts will be performed using FACS Calibur (BD Biosciences, USA)
- The pro inflammatory biomarkers profile will be analyzed using customized BDTM Cytometric Bead Array (CBA) (BD Biosciences, San Jose, California). Individual plex assay for Human P-selectin and sCD14 will be used to configure a multiplex system for quantitation of the targeted biomarkers simultaneously.
- T cell activation and exhaustion will be determined as follows: PBMCs will be thawed and stained with live and dead fixable yellow (Invitrogen, Carlsbad, CA). Then aliquots of the stained cells will be further stained with CD3 PerCP (BioLegend, San Diego, CA), CD4 AF700, CD8 APC-H7, HLA-DR PE, CD38 APC, and PD-1 BV421 (BD Biosciences, San Jose, CA) and with CD14 Pacific Blue, CD16 PE, and CD69 PE-Cy7 (BD Biosciences, San Jose, CA) and acquired on an LSRII flow cytometer (BD Biosciences, San Jose, CA), using FACS Diva software. Percentages of activated (CD38+HLA-DR+) and exhausted (PD1+) CD4

and CD8 T cells and monocyte subsets (CD14/CD16/CD69) will be determined by gating based on isotype controls using FacsDiva software (BD Biosciences, San Jose, CA).

Performance of the various laboratory tests will be done according to the SOPs in the laboratories and interpretation of results will be in line with the instructions of the manufacturers of the respective test kits/systems.

A total of 20 ml of whole blood will be drawn from each patient in three portions. i.e. 1) 4ml in one K2 EDTA tubes for FBP and CD4 count, 2) 12mls in four K2 EDTA tubes for plasma (viral load and platelet and monocyte activation biomarkers) and PBMCs (T cell activation and exhaustion) separation and 3) 4 ml in one red topped tube for lipid profile, RFT and LFT. All sample portions will be transported in a cool box at room temperature by motorcycle to the MCRL for processing, storage and analysis. Time allowable from sample collection to processing of FBP and CD4 count is 6 hours. At the laboratory, 50 microliters will be used for FBP and 50 microliters for CD4 count.

For plasma and PBMCs separation, 12 ml sample portion will be centrifuged to separate plasma (at 1500 X g for 10 minutes at minimum acceleration and deceleration) within 2 hours from the time of sample collection. Separated plasma (approximately 6 ml) will be stored in 1.5ml and 4.5ml portions and immediately stored at -80° Celsius. 1.5ml portion will later be used for viral load testing while the 4.5 ml portion will be transported to Kumamoto University-Japan for platelet and monocyte activation biomarkers testing.

PBMCs will be separated from cellular sediment of whole blood obtained from plasma separation procedure above (see appendix 10) and then stored at -80° Celsius to be transported to Kumamoto University-Japan for T cell activation and exhaustion analysis. Lipid profile, RFT and LFT, will be tested from serum obtained from centrifugation (at 2500 revolutions per minute for 15 minutes) of the last 4 ml sample portion (in red topped tube) The time allowable from sample collection to processing is 6 hours. The obtained serum will be stored at - 80° Celsius awaiting analysis. All the frozen samples will slowly be brought to room temperature at the time of analysis.

#### **2.11.7 Other assessments**

During clinical evaluation at each monthly visit, the attending clinician will look for occurrence of any AE since the last visit and all the AEs will be recorded in a specially designed form.

Assessment of compliance to study drugs will be by pill count. Patients' remaining monthly tablets of their study drugs will be counted to ascertain compliance at each monthly follow up visit. Overall compliance will be the average of the monthly compliances.

Adherence to ART will be measured based on pill counts. Patients' will be asked to return with the ARV drug bottles every time they come to the clinic for their follow up visits. At each visit, pills remaining in bottles will be counted by the study doctor and the percentage of these pills to the dispensed pills during the previous visit will be calculated based on the dose and the number of days dispensed. The pill count adherence percent will be obtained by dividing the number of pills consumed by the total number of pills dispensed at the last visit and multiplied by 100. Overall adherence will be the average of the monthly adherences. For patients who will not last in the study for all the 6 months, their adherence to ART will be calculated by taking the average of the monthly adherences of months they have been in the study. Greater than 90% overall adherence by pill count will be considered adherence(58).

Morbidity will be defined as health care facility visits for medical attention/ care because of illness and/or the number of admissions to a health care facility/ hospital. At each monthly visit, patients will be asked if they visited any health care facility to seek medical care/ treatment and/ or if they were admitted on medical basis since last visit. The reason for visit or admission will be traced from the patient or medical and/or clinical records respectively.

All-cause mortality will be defined as confirmed death of any cause with certification of death by medical practitioner or a verbal or telephone confirmation of death from a relative or friend. Clinical conditions associated with death will be determined by verbal autopsy and/or review of clinic and hospital records. Formal autopsies will not be conducted. Conditions will be defined as associated with death if they will be diagnosed within one month prior to or at time of death or were thought to be related to death after review of the medical records. More than one diagnosis will be possible for each death.

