**Definitions.**

1. **Adherence to ART** will be defined as greater than 90% adherence by pill count.
2. **Adverse Event (AE)** will be defined as any untoward medical occurrence in a patient enrolled into this study regardless of its causal relationship to study treatment.
3. **Serious Adverse Event (SAE)** will be defined as any AE that results in death; or is immediately life threatening; or requires inpatient hospitalization; or requires prolongation of existing hospitalization; or results in persistent or significant disability/incapacity; or is a congenital anomaly/birth defect.
4. **Non-Serious Adverse Event** will be defined as any AE that does not result in death; or is not immediately life threatening; or does not require inpatient hospitalization; or does not require prolongation of existing hospitalization; or does not result in persistent or significant disability/incapacity; or is not a congenital anomaly/birth defect.
5. **Suspected Unexpected Serious Adverse Reaction (SUSAR)** will be defined as any SAE that is both suspected to be related to the study treatment and is unexpected (i.e. not consistent with applicable product information).
6. **Morbidity** will be defined as number of health facility/ hospital visits for medical attention/ care because of illness and/or number of health facility/ hospital admissions.
7. **All- cause mortality** will be defined as confirmed death of any cause with certification of death by medical practitioner or a verbal or telephone confirmation of death from a relative or friend.
8. **Clinical conditions associated with death** will be defined as those clinical conditions diagnosed within one month prior to or at time of death or were thought to be related to death after review of the medical records.
9. **Low- dose- aspirin (ASA)** will be defined as ASA dosages between 75mg and 325mg taken every day.
10. **Compliance to ASA** will be defined as adherence to ASA therapy for at least 22 days in a month.

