#### **1.4 Rationale**

Since initiation of treatment and care of HIV-infected patients in Tanzania and scaling-up of treatment to reach populations in all settings in the country, parallel efforts have been made to improve compliance to treatment. As observed in the foregone literature review it is prudent to establish the potential benefit of adding ASA in the current ARV treatment regimen in the country and also investigate the impact of adding ASA on treatment adherence. The goal is to establish strategies for enhancing ART impact and further improving treatment outcome. ASA is a cheap drug that is easily available in Tanzania and once its beneficial effect is confirmed its use in ART therapy can be easily implemented in the current National HIV treatment programme.

Findings from this proposed study will provide preliminary data for policy makers especially in the Ministry of Health, Community Development, Gender, Elderly and Children (MoHCDGEC) on the possibility of adding ASA to the conventional ARV treatment in the HIV- infected individuals to reduce morbidity and mortality. Hence, this proposed study will provide preliminary data for future consideration for ASA use in HIV care and treatment.

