#### E. ADHERENCE TO ART

Number of pills returned: \_\_\_\_

Start date of drug for this period: \_\_/\_\_/\_\_\_\_

Stop date of drug for this period: \_\_/\_\_/\_\_\_\_

| Number of pills that should have been taken | Number of Pills remaining | Number of pills actually taken | % of Pills taken |
|---------------------------------------------|---------------------------|--------------------------------|------------------|
|                                             |                           |                                |                  |
| Comments                                    |                           |                                |                  |

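### ART adherence in 2.11.7 is scored against pills dispensed, not pills due between visits, so the >90% classification depends on visit timing and conflicts with the CRF

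*Protocol*

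**What the plan says.** Section 2.11.7 measures ART adherence by pill count at each monthly visit. The monthly percentage is "obtained by dividing the number of pills consumed by the total number of pills dispensed at the last visit", times 100. The same paragraph says that the percentage of remaining pills is "calculated based on the dose and the number of days dispensed", which refers to the days supplied and not the days elapsed. The monthly values are then combined: "Overall adherence will be the average of the monthly adherences". For patients who do not complete six months, the overall value comes from "taking the average of the monthly adherences of months they have been in the study". A patient is adherent when the overall value is above 90%, and the Definitions page gives the same threshold: "greater than 90% adherence by pill count".

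The dispensing pages of the CRF (Appendices 2 and 3) describe a thirty-day ARV supply. Section 2.6 says that patients are seen monthly, and the protocol states no visit window.

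Appendix 3, section E, is laid out differently. It records a start and a stop date for the period and has a column headed "Number of pills that should have been taken", beside columns for pills remaining, pills actually taken and the percentage taken.

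**The concern.** Pills dispensed equal pills due only when the visit falls exactly on day 30. On an earlier visit the patient properly still holds pills, and the formula treats them as missed. On a later visit the patient may have run out, and the formula cannot see the uncovered days. The percentage therefore mixes pill-taking with appointment timing, and the strict cut-off turns that into a classification error.

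The CRF layout points to the other denominator. The same patient can get two percentages from one visit, and nothing says which one is analysed. Adherence is named in the broad objective, and secondary objective 8 is to determine its level, so an error in the level falls directly on what that objective reports.

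**Working it through.** The plan states no computed adherence figure, so there is none to reproduce. The check applies the 2.11.7 formula directly.

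**Inputs.** Supply: 30 days (CRF dispensing pages). Cut-off: strictly above 90% (Definitions; 2.11.7). Overall value: unweighted mean of the monthly values (2.11.7). Assumed: one pill a day, exactly 30 dispensed and, except in the last step, no carry-over of leftover pills.

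**Formulas.** Protocol value = pills consumed / 30. Comparison value = pills consumed / days elapsed, which is the reading that the CRF columns suggest.

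**Perfect taker seen early**

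| Interval (days) | Protocol value | Pills taken / pills due |
|---|---|---|
| 26 | 26/30 = 86.7%, fails | 100% |
| 27 | 27/30 = 90.0%, fails | 100% |
| 28 | 28/30 = 93.3%, passes | 100% |
| 29 | 29/30 = 96.7%, passes | 100% |

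With no interval above 30 days, the overall value is the mean interval divided by 30. A perfect taker therefore fails when the mean interval is 27 days or less. For example, two 24-day and four 28-day intervals give (2 × 24 + 4 × 28) / 180 = 160/180 = 88.9%.

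**Good but imperfect taker on a 28-day cycle**

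- One missed dose in an interval: protocol 27/30 = 90.0%, fails. Against pills due: 27/28 = 96.4%.
- Six intervals: 180 pills dispensed, 168 due. The written rule needs more than 0.90 × 180 = 162, so at least 163. That is 163/168 = 97.0%, with 5 misses allowed.
- The stated cut-off applied to pills due needs more than 0.90 × 168 = 151.2, so at least 152. That is 152/168 = 90.5%, with 16 misses allowed.

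**Late attender who takes all 30 pills**

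| Return day | Protocol value | Pills taken / pills due |
|---|---|---|
| 33 | 100% | 30/33 = 90.9% |
| 34 | 100% | 30/34 = 88.2% |
| 35 | 100% | 30/35 = 85.7% |
| 40 | 100% | 30/40 = 75.0% |

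From day 34 the written rule passes a patient whose coverage is below the cut-off.

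**Carry-over.** Suppose that consumed is read as pills dispensed minus pills remaining. A perfect taker on 27-day intervals holds 3 pills after the first interval and 6 after the second. The second month then scores (30 − 6)/30 = 80.0%, so uncounted leftovers make the error larger.

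**The case against.** The strongest reply is that the clinic calendar does not produce the extreme cases. Section 2.6 reserves Fridays and Saturdays for paediatric patients and adolescents. If adult clinics run Monday to Thursday (an assumption), day 30 falls on a Wednesday, Thursday, Friday or Saturday. Moving a Friday or Saturday back to Thursday gives 29 or 28 days, and moving it forward to Monday gives 33 or 32. On those intervals a perfect taker scores at least 93.3% and passes, and one who takes 30 pills in 33 days is passed correctly. This stands: a reader might infer that the four-day adult week causes 27- or 35-day intervals, but the protocol does not support that. Such intervals would need another cause, on which it gives no data. The reply does not remove the 28-day result, where the effective cut-off is 97.0%.

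It can also be said that the CRF already holds the right columns. It does, but it writes out no formula, while 2.11.7 writes out a different one. The CRF makes the repair cheap without settling the conflict.

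Finally, under randomisation and blinding there is no stated reason for visit timing to differ by arm. The error should therefore mainly distort the level in both arms rather than create a difference between them. That also stands and limits the weight of the point.

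**Conclusion.** The denominator in 2.11.7 is wrong as written and conflicts with Appendix 3. The size depends on visit intervals that the protocol does not fix: on a constant 28-day cycle the rule demands 97.0% of doses instead of more than 90%, and from day 34 it passes patients with coverage of 88.2% or less. These figures assume one pill a day and a thirty-day supply. The consequence is a misreported level of a secondary outcome. The primary outcome and the sample size are untouched.

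Two stronger readings are not supported.

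- A reader might infer that drop-outs are generally counted as adherent. Under 2.11.7 a patient who leaves must still exceed 90% in the months counted, and 2.9.6.1 and 2.9.6.2 keep withdrawn patients in follow-up to six months where possible. The rule matters mainly for patients lost to follow-up. Averaging over the months in study is an openly stated choice; how to score later months is a debatable missing-data question.
- A reader might infer that the comparison is meant to show the effect of an added tablet, because section 1.4 says that the study will "also investigate the impact of adding ASA on treatment adherence" and both arms add one tablet. Secondary objective 8 and research question 9 ask for the level of adherence in patients taking ASA or placebo. The looser wording of 1.4 is a separate matter of interpretation, not part of this error.

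**What to change.** In 2.11.7, replace the denominator. Define monthly adherence as pills taken divided by pills due between the two visit dates (daily dose times days elapsed). Define pills taken as pills carried forward plus pills dispensed minus pills remaining. State that this is the percentage in Appendix 3, section E, and apply the >90% cut-off to it. The CRF states no cap at 100%, so if one is wanted it has to be written in.

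The average over months in the study may stay. Report with it the number of months that contribute for each patient, and state that it does not describe adherence after loss to follow-up.

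The cost is a few sentences in 2.11.7. Visit dates and pill counts are already on the CRF, so no new data are needed. The reported level may move either way: up for patients seen early, down for those seen late.

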### **1.6.3 Secondary objectives**

The secondary objectives of the proposed study are:

1. To compare the CD4 counts measured at 3 and 6 months among HIV- infected individuals after initiating ARV therapy alone or ARV therapy and 75mg ASA.
2. To compare the plasma levels of immune activation biomarker (sCD14) measured at 3 and 6 months among HIV- infected individuals after initiating ARV therapy alone or ARV therapy and 75mg ASA.
3. To compare the plasma levels of platelet activation biomarker (P- selectin) measured at 3 and 6 months among HIV- infected individuals after initiating ARV therapy alone or ARV therapy and 75mg ASA.
4. To compare percentage of activated T cells (CD38 positive and HLA-DR positive T cells) measured at 3 and 6 months among HIV- infected individuals after initiating ARV therapy alone or ARV therapy and 75mg ASA.
5. To compare percentages of exhausted T cells (PD1 positive T cells) measured at 3 and 6 months among HIV- infected individuals after initiating ARV therapy alone or ARV therapy and 75mg ASA.
6. To compare morbidity among HIV- infected individuals initiating ARV therapy alone or ARV therapy and 75mg ASA.
7. To compare all-cause-mortality among HIV- infected individuals initiating ARV therapy alone or ARV therapy and 75mg ASA.
8. To determine level of adherence to ARV therapy among HIV- infected individuals initiating ARV therapy and ASA or placebo.

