## H. MORBIDITY

Start date of assessment for this period: \_\_/\_\_/\_\_\_\_

Stop date of assessment for this period: \_\_/\_\_/\_\_\_\_

|                                             | Number of hospital/ health facility visits | Number of hospital/ health facility admissions |
|---------------------------------------------|--------------------------------------------|------------------------------------------------|
|                                             |                                            |                                                |
| Reasons for visit or admission respectively |                                            |                                                |

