#### 6.4 Appendix 4 – Death Report Form

(Please complete this form only when death of the participant is reported)

Participant study number \_ \_ \_ \_ \_

Date of completion of the form \_ / \_ / \_ \_ \_ \_

**Date of Death** \_ / \_ / \_ \_ \_ \_

|                                                    |                 |  |                       |  |
|----------------------------------------------------|-----------------|--|-----------------------|--|
| Place of death                                     | 1. Hospital     |  | Other(specify)        |  |
| Autopsy performed?                                 | YES             |  | NO                    |  |
| Cause of death/
condition associated with death | Study treatment |  | Other, please specify |  |
| Comments                                           |                 |  |                       |  |

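### No route carries an illness visit or admission between the last attended visit and death into the morbidity count

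*Protocol*

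**What the plan says.** Morbidity is a between-arm comparison. Secondary objective 6 in section 1.6.3 reads "To compare morbidity among HIV- infected individuals initiating ARV therapy alone or ARV therapy and 75mg ASA", and section 2.7 lists morbidity among the secondary clinical responses. Definitions item 6 sets it as "number of health facility/ hospital visits for medical attention/ care because of illness and/or number of health facility/ hospital admissions". Nothing there excludes an admission that ends in death.

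How the events are found is set in section 2.11.7: "At each monthly visit, patients will be asked if they visited any health care facility to seek medical care/ treatment", together with a question about medical admissions since the last visit. In that paragraph, records serve to trace the reason for a visit or admission. Section 2.10 and Table 2.1 likewise place the morbidity check at the monthly visits.

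The counts are entered in section H of the follow-up CRF (Appendix 3). It has one column for visits and one for admissions, and is dated by fields such as "Start date of assessment for this period".

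For deaths, Appendix 4 instructs "Please complete this form only when death of the participant is reported". The form holds the date and place of death, whether an autopsy was done, cause or associated condition, and comments. Section 2.11.7 adds "Clinical conditions associated with death will be determined by verbal autopsy and/or review of clinic and hospital records".

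**The concern.** The collection rule depends on the patient returning to answer. Take a patient who is well at the month 2 visit, is admitted three weeks later and dies in hospital. The definition counts that admission. The procedure that fills section H would have run at month 3, and there is no month 3 visit. The form that is completed instead asks where and why the patient died, but not how many visits or admissions came before.

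These are among the most severe illnesses in the trial, and whether they are missed depends on death, which is itself an outcome. If one arm has more deaths, it also has more final intervals with no morbidity data, so its recorded morbidity is pulled down relative to the other arm. Section 1.4 presents reduced morbidity and mortality as the purpose of adding aspirin (ASA), so the two results will be read together.

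**Working it through.** The protocol states no rate, effect size or power for morbidity, so there is no figure of its own to reproduce. The check is mainly textual, followed by an illustration of scale.

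**Following an admission between the last attended visit and death through the protocol**

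| Place | What it does | Brings the admission into the morbidity count? |
|---|---|---|
| Definitions, item 6 | Counts illness visits and admissions | Included by definition |
| 2.11.7, morbidity | Asks the patient at the next monthly visit; records give the reason | No, the patient cannot be asked |
| Appendix 3, section H | Takes the two counts, on the follow-up visit CRF | No instruction to complete it at death |
| Appendix 3, section I (off-study form) | Lists death as a reason for leaving | No link to section H |
| Appendix 4 (Death Report Form) | Date, place, autopsy, cause, comments | No count of visits or admissions |
| 2.11.7, mortality | Verbal autopsy and/or record review | Used for conditions associated with death |
| 2.12.1 and 2.12.4.1 | Hospitalization and death are SAEs, reported within 24-72 hours | Held as safety data, not linked to morbidity |
| 2.14.1 | Names medical files as a general data source | Not linked to morbidity |

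The event is inside the definition, and several sources may hold it, but none is directed to the morbidity outcome. By contrast, section 2.11.7 does say what to do about adherence for patients who do not stay the full six months: average the months they were in the study. It has no counterpart for morbidity.

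**Scale, by assumption**

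Input from the protocol: n = 227 per arm (section 2.13.1). Assumed: six-month mortality d, the share of deaths in hospital h, and one terminal admission per hospital death, beginning after the last attended visit.

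Affected admissions per arm = n × d × h.

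- d = 2%, h = 50%: 227 × 0.02 × 0.5 = 2.3
- d = 4%, h = 70%: 227 × 0.04 × 0.7 = 6.4
- Wide limits: 227 × 0.01 × 0.5 = 1.1 and 227 × 0.10 × 1.0 = 22.7

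A between-arm bias arises only from the difference in deaths. With 2% mortality in one arm and 4% in the other, and the same h in both, the difference in affected admissions is 227 × 0.02 × h: 2.3 at h = 50% and 3.2 at h = 70%.

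As a share of all admissions, the affected fraction is d × h / (a + d × h), where a is the number of admissions per patient recorded at attended visits, also assumed:

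- a = 0.10: 0.010/0.110 = 9% to 0.028/0.128 = 22%
- a = 0.30: 0.010/0.310 = 3% to 0.028/0.328 = 9%

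The share depends heavily on a, for which the protocol gives no value, so the absolute count is the safer description. Outpatient illness visits in the same interval would be additional and are not included.

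**The case against.** The strongest reply is that the information is not lost to the trial. Hospitalization and death are each SAEs, and reporting does not wait for a monthly visit. The Death Report Form records whether death was in hospital and has a comments field. Records may be reviewed after death, and medical files are a general data source. All-cause mortality is analysed in its own right. How a count outcome handles follow-up cut short by death is normally a matter for the statistical analysis plan.

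Much of this stands. It means that the death is counted, that the admission can often be recovered, and that the repair is easy. It does not close the gap, because no section sends any of these sources to the morbidity count. An analysis plan can choose how to treat the interval, but it cannot supply counts that the CRF did not ask for. Place of death gives no number of visits or admissions. Since section 2.11.7 joins verbal autopsy and record review by and/or, records need not be examined for every death.

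Two stronger readings might be inferred, and the documents support neither.

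- *Every fatal admission is scored as zero.* No section gives a scoring rule for the interval, so it could equally be treated as missing or filled from another source. An admission already reported at an attended visit is in the count.
- *The and/or in the definition gives one illness two scores.* Section H records visits and admissions in separate columns, and nothing in the protocol adds them. A clinic visit followed by admission is recorded as one of each. Whether to report the two separately or combine them is commonly left to the analysis plan.

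**Conclusion.** The point holds as a gap in data collection. Events between the last attended visit and death fall within the morbidity definition but have no stated route into the count, so their value is undefined: missing or zero. Recorded morbidity may therefore be too low in whichever arm has more deaths.

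The size is unknown. The figure of about 2-6 affected admissions per arm rests wholly on assumed mortality of 2-4%, 50-70% of deaths in hospital, and one admission per hospital death starting after the last attended visit. The bias between arms would be smaller than that, and absent if deaths and the circumstances of dying were balanced. The calculation does not show that morbidity and mortality would in fact point in opposite directions.

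This concerns one of several secondary outcomes. It is a worthwhile and cheap improvement, not a threat to the primary analysis.

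**What to change.** In section 2.11.7 and in Appendix 4, require section H of the CRF to be completed at every reported death, for the period from the last attended visit to the date of death. Name the sources: the next-of-kin contact or verbal autopsy, whatever clinic and hospital records are available, and the SAE report. Recording which source was used would let the analysis separate proxy or record data from patient report.

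The cost is a sentence in section 2.11.7, and an instruction with two count fields on the Death Report Form (or a cross-reference to section H). No new study visits are needed. There are two drawbacks. Proxy and record data are less complete than patient report, and records may have to be checked for some deaths where only a verbal autopsy was planned. The change is best made before data collection, because counts not sought at the time of death may be hard to recover later.
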